### Secondary outcomes

90-day all-cause mortality and MAKE-14: Analysis will be as described above for 14-day all-cause mortality.Time-to-event data will be displayed as Kaplan–Meier curves and log-rank tests will be used to test for significant differences between the two treatment groups (Fig. 3, Figure S6). For time to death, hazard ratios will be estimated with Cox proportional hazards regression, with a random effect for site and fixed effects for the exposure adjusted for the time between T0 (initiation of vasopressor therapy) and randomisation, vasopressor dose, APACHE III score at randomisation and type of shock.

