### Sample size

Based on our pilot feasibility study [11] and prospective cohort study [8], a sample size of 1260 is required to demonstrate an absolute risk reduction of 6% in the primary endpoint (14-day mortality) in the intervention arm, assuming a 20% incidence of 14-day mortality in the control arm, at an alpha level of 0.05 and power of 80% and allowing for 2.5% attrition. The absolute risk difference of 6% is a conservative estimate relative to the effect size observed in our feasibility study (14-day mortality rate of 13% versus 6% in the standard care versus individualised blood pressure target) [11] or the effect size observed in a pre-specified comparative analysis in our prospective cohort study (14-day mortality rate of 13% versus 22% (*p* = 0.04) in the group with lower-than-median blood pressure deficit versus the group with higher-than-median blood pressure deficit) [8].

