Serum lactate at randomisation, median [IQR], mmol/l		
Pre-illness serum creatinine, median [IQR], micromole/l		
Serum creatinine at randomisation, median [IQR], micromole/l		
Intravenous fluid given within 24 h prior to randomisation, median [IQR], ml		
Fluid balance at randomisation, median [IQR], ml		
Exposure to nephrotoxic agents within 72 h prior to randomisation, *n* (%)		
ACE inhibitor or angiotensin receptor blocker		
Intravenous contrast		
Non-steroidal anti-inflammatory drug		
Aminoglycoside		
Vancomycin		
Calcineurin inhibitor		
Gancyclovir		
Remdesivir		
Number of nephrotoxic agents within 72 h prior to randomisation, median per patient [IQR]		
Time from ICU admission to randomisation, median [IQR], h		
Time from T0^§^ to randomisation, mean (SD), h		

*IQR* interquartile range, *APACHE* Acute Physiology and Chronic Health Evaluation, *BP* blood pressure,

*MAP* mean arterial pressure, *ACE* angiotensin converting enzyme

^§^ T0—Time-point, when vasopressor or inotrope support was initiated

**Table 3 Tab3:** Exposure variables and other process of care measures

Characteristics	Standard MAP (*n* = xxx)	Individualised MAP (*n* = xxx)
Target MAP on randomisation, median [IQR], mmHg		
MAP-deficit^*^ (time-weighted average), median [IQR], %		
Percentage of time spent with > 20% MAP-deficit^**χ**^, median [IQR], %		
Achieved MAP ^#^ during the treatment period, median [IQR], mmHg		
Time-weighted average vasopressor dose (noradrenaline-equivalent), median [IQR], mcg/kg/min		
Time from randomisation to cessation of vasopressors, median [IQR], h		
Exposure to nephrotoxic agents within 14 days after randomisation, *n* (%)		
ACE inhibitor or Angiotensin receptor blocker		
Intravenous contrast		
Non-steroidal anti-inflammatory drug		
Aminoglycoside		
Vancomycin		
Calcineurin inhibitor		
Gancyclovir		
Remdesivir		
Number of nephrotoxic agents within 14 days after randomisation, median per patient [IQR]		
Exposure to blood transfusion within 5 days after randomisation, *n* (%)		
ICU length of stay post randomisation among survivors, median [IQR], days		
Hospital length of stay post randomisation among survivors, median [IQR], days		

*IQR* interquartile range, *MAP* mean arterial pressure, mmHg

^*****^ MAP-deficit = [(pre-illness MAP − achieved MAP)/pre-illness MAP] × 100, using positive incremental area-under-the-curve of MAP-deficit during vasopressor therapy

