### Primary outcome

Effect estimates for 14-day all-cause mortality will be derived from multivariable logistic mixed effects models with a random intercept for site (assumed normally distributed on the logit scale, with a constant variance) to account for clustering within sites and fixed effects for treatment group, time between T0 (initiation of vasopressor therapy) and randomisation, APACHE III score at randomisation, noradrenaline-equivalent dose at randomisation and type of shock (Table 4). A two-sided *P*-value for the effect of treatment will be obtained from this model and values < 0.05 will be considered statistically significant. The effect estimates of interest will be the relative risk and risk difference (individualised care versus standard care). The relative risk estimate will be obtained as a ratio of the mean for each group of the individual predicted probabilities obtained from the logistic regression model. Differences of these means will be the risk difference. Bootstrapping, using 10,000 iterations, will be used to calculate 95% confidence intervals.

**Table 4 Tab4:** Outcome measures

	Standard MAP (*n* = xxx)	Individualised MAP (*n* = xxx)	Adjusted^*^ relative risk (95% CI)	Adjusted^*^ risk difference (95% CI)	*P* value
Day 14 all-cause mortality, *n* (%)					
Major Adverse Kidney Event^δ^ within 14 days of randomisation, *n* (%)					
- New requirement for RRT					
- Doubling of creatinine					
RRT- free days^#^ by day 28, *n* (%)					
Day 90 all-cause mortality, *n* (%)					

*RRT* renal replacement therapy

^*^ The model included random intercepts for sites and fixed effects for treatment group, the time between T0 (initiation of vasopressor therapy) and randomisation, APACHE III score at randomisation, vasopressor dose at randomisation and type of shock

^**δ**^ Major adverse kidney event (MAKE)−14 was a composite outcome of death, or new renal replacement therapy during the first 14 days, or doubling of serum creatinine from pre-illness level on day 14 or on day of discharge from ICU, whichever was earlier

^#^ Patients who died were assigned the worst score of − 1

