**Fig. 3 Fig3:**
[figure not shown]
Time-to-event figure for day 14 mortality. The number of people at risk in each group will be listed for days 0, 7 and 14. Cox regression analysis with random effect for site and fixed effects for the exposure adjusted for the time between T0 (initiation of vasopressor therapy) and randomisation, vasopressor dose, APACHE III score at randomisation and type of shock will be usedRRT-free days by day 28 will be defined as the number of days in the first 28 days post-randomisation when the participant was alive and not dependent on RRT. RRT-free days by day 28 will be analysed as an ordinal outcome, with death assigned the worst value (− 1). Comparisons between groups will be made using a mixed effects proportional odds regression model, with the same fixed and random effects as per the primary outcome model.

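### The MAKE-14 model omits baseline creatinine, although patients already past doubling can enter and both creatinine values are collected: a loss of precision, not a bias

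*Protocol article*

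**What the plan says.** Under Secondary outcomes the article states: "90-day all-cause mortality and MAKE-14: Analysis will be as described above for 14-day all-cause mortality". The model referred to, under Primary outcome, is a logistic mixed model with a random intercept for site and fixed effects for treatment, time from T0 to randomisation, APACHE III, noradrenaline-equivalent dose and type of shock. The Table 4 footnote repeats this list, and the table gives adjusted columns to MAKE-14 and to its RRT and creatinine rows. RRT-free days is analysed by proportional odds regression "with the same fixed and random effects as per the primary outcome model".

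Under Outcomes, the creatinine component of MAKE-14 is a doubling relative to the premorbid value, and a rule is given for estimating that value when no record exists. The renal exclusions are current or imminent RRT, a creatinine rise above 350 μmol/l, and end stage renal disease. Data collection lists premorbid creatinine and creatinine at randomisation, and Table 2 tabulates both, the latter as "Serum creatinine at randomisation, median [IQR], micromole/l". Acute kidney injury appears only as a subgroup factor for 14-day mortality.

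**The concern.** The creatinine component is judged against the premorbid level, not the level at randomisation. A patient whose creatinine has already doubled at entry starts above the threshold and avoids that component only by recovering. The Table 4 footnote reads creatinine on day 14 or at ICU discharge, whichever is earlier, which can shorten the time available to recover. The ratio of randomisation to premorbid creatinine is thus the baseline value of an outcome component, and no kidney outcome model uses it.

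Randomisation is stratified by site only, so baseline kidney function is balanced by chance alone. What is at stake is the precision of the MAKE-14 comparison. MAKE-14 is a secondary outcome, but the hypothesis in the Introduction names major adverse kidney events beside 14-day mortality.

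**Working it through.** **Step 1. The plan's own figure.** The plan says "a sample size of 1260 is required to demonstrate an absolute risk reduction of 6% in the primary endpoint". It takes control-arm mortality as 20% and works "at an alpha level of 0.05 and power of 80% and allowing for 2.5% attrition". With a two-sided test (Primary outcome: "values < 0.05 will be considered statistically significant"), p₁ = 0.20, p₂ = 0.14 and mean 0.17:

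n per arm = [1.96·√(2·0.17·0.83) + 0.8416·√(0.20·0.80 + 0.14·0.86)]² / 0.06² = (1.0412 + 0.4457)² / 0.0036 ≈ 614.1, so 615.

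The total is 1230, and 1230 / 0.975 = 1262 against 1260 stated. This reproduces. It rests on mortality and is unaffected here. No power is stated for MAKE-14.

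**Step 2. Can a patient enter already doubled?** The highest creatinine allowed by the 350 μmol/l limit is premorbid + 350.

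| Premorbid (μmol/l) | Highest allowed | Ratio |
|---|---|---|
| 60 | 410 | 6.8 |
| 80 | 430 | 5.4 |
| 100 | 450 | 4.5 |
| 200 | 550 | 2.75 |

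For any premorbid value below 350, a patient past doubling can satisfy this limit. The exclusion of imminent RRT may remove some of them. The documents do not say how many remain.

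**Step 3. Variance explained (assumed inputs).** Let q be the share already doubled, p the overall MAKE-14 risk, and p₁ and p₀ the risks in those already doubled and the rest, fixed by p, q and a prognostic odds ratio (OR). Then R² = q(1−q)(p₁−p₀)² / [p(1−p)], the SE falls by 1 − √(1−R²), and the equivalent gain in patients is 1/(1−R²) − 1. Each cell gives p = 25% / 35%.

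| q | OR | R² | SE cut (%) | Equivalent extra patients (%) |
|---|---|---|---|---|
| 10% | 3 | 0.028 / 0.028 | 1.4 / 1.4 | 2.9 / 2.9 |
| 10% | 8 | 0.105 / 0.089 | 5.4 / 4.5 | 11.7 / 9.7 |
| 20% | 3 | 0.045 / 0.048 | 2.3 / 2.4 | 4.8 / 5.1 |
| 20% | 8 | 0.169 / 0.160 | 8.8 / 8.4 | 20.3 / 19.1 |
| 30% | 3 | 0.054 / 0.061 | 2.7 / 3.1 | 5.7 / 6.5 |
| 30% | 8 | 0.189 / 0.204 | 9.9 / 10.8 | 23.3 / 25.6 |

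On 1260 patients the extremes are about 36 and 322.

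**Step 4. Power with a severity covariate already in the model.** Logistic simulation with n = 1228 (1260 × 0.975), 800 runs, control-arm MAKE-14 35% and treatment OR 0.72. One severity score (OR 1.8 per SD) stands in for the planned covariates; site is not modelled. Power is shown without → with the already-doubled indicator, where r is the correlation between severity and the scale underlying baseline doubling.

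| q | OR | r = 0 | r = 0.4 |
|---|---|---|---|
| 10% | 3 | 71.0 → 73.8% | 70.5 → 72.9% |
| 10% | 8 | 64.8 → 68.8% | 63.9 → 68.9% |
| 20% | 3 | 70.4 → 71.5% | 70.0 → 72.6% |
| 20% | 8 | 60.0 → 68.5% | 57.3 → 64.3% |
| 30% | 3 | 69.3 → 72.8% | 68.6 → 71.0% |
| 30% | 8 | 55.5 → 65.5% | 51.1 → 61.0% |

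Gains run from 1.1 to 10.0 points. Simulation error is about 1.7 points on each power figure, and both models were fitted to the same data sets.

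**Step 5. Bias.** The mean risk differences with and without the indicator are never more than 0.0006 apart (for example −0.0587 in both at q = 20%, OR 8, r = 0). Only the spread changes: at q = 30%, OR 8, r = 0.4 the SD falls from 0.0264 to 0.0240, and (0.0264/0.0240)² = 1.21.

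**The case against.** The strongest reply is that nothing here is invalid. Under concealed 1:1 randomisation a pre-specified covariate set gives a sound comparison whatever prognostic variables it omits, and one common model for all outcomes is a defensible choice. That stands: this is a gain to be had, not an error in inference.

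Three stronger readings are tempting, and the documents support none of them.

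- **That the MAKE-14 result would be biased, or exposed to harm from chance imbalance.** With 630 per arm the 95% range of chance imbalance in the share already doubled, 1.96·√(2q(1−q)/630), is ±3.3 points at q = 10% and ±5.1 at q = 30%. The confidence interval already allows for this. It is the same precision loss seen from another side.
- **That baseline creatinine is the main determinant.** Death is part of MAKE-14. At the assumed 20% control mortality and a MAKE-14 rate of 25–35%, deaths would be 80% to 57% of events (20/25 and 20/35), so the severity covariates matter too.
- **That RRT-free days has the same flaw.** Nobody on RRT may enter and the outcome has no creatinine criterion, so the argument about already meeting the threshold does not apply.

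It is also fair to say that the upper end is demanding. At q = 30%, OR 8 and a 35% rate, risk in those not yet doubled is 21%, close to the 20% mortality assumed for the whole control arm. Deaths would have to concentrate among those already doubled.

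Two replies do not stand. The covariate list is not left to an unseen plan: the article presents itself as the analysis plan and fixes the list twice. And APACHE III may carry some renal information, but the documents do not say how much, and one overall score does not replace the ratio to premorbid creatinine.

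**Conclusion.** The point holds as a matter of efficiency in one secondary outcome. The plan fixes a MAKE-14 model without any kidney baseline, although the outcome's creatinine threshold can be passed before randomisation and the data to adjust for it are collected. The planned estimate is unbiased, and the primary outcome and the sample size of 1260 are untouched.

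The size rests wholly on assumptions, because the documents give no MAKE-14 rate, no share already doubled and no prognostic strength. Over the ranges in the working the gain is about 1 to 10 power points, or roughly 3% to 26% more patients. At the low end it is small. It shrinks as the planned covariates overlap with kidney function; the moderate overlap simulated (r = 0.4) still left gains of 2.4 to 9.9 points.

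**What to change.** Before treatment allocation is unblinded, pre-specify log(creatinine at randomisation / premorbid creatinine) as an added fixed effect in the models for MAKE-14 and for its creatinine and RRT components. Use the existing rule under Outcomes where premorbid creatinine must be estimated, and state a simple imputation for any missing randomisation creatinine so that the complete-case approach drops no patient. Amend the Table 4 footnote to match. Leave the mortality models and the entry criteria as they are.

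The MAKE-14 relative risk and risk difference are built from averaged predicted probabilities, so the added term does not change what they estimate. Adding it to the RRT-free-days model is optional and would rest on general prognostic value only. There the odds ratio is conditional on the covariates, so its scale would change and the choice must be made in advance.

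The cost is one extra covariate and some plan wording, with no new data and no more patients. The downside is some measurement error in the covariate where premorbid creatinine is estimated. Recruitment is expected to run to 2028, so the change can still be made in advance; made after unblinding, the same adjustment would look data-driven.

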### Randomisation

Randomisation will be undertaken centrally in a concealed fashion, with a unique computer-generated, site stratified, permuted block randomisation method with random block sizes of 4 and 6. Enrolled patients will be randomly allocated in a 1:1 ratio to either standard care arm or intervention arm.

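### Time to death: significance comes from a log-rank test with no covariates named, while the hazard ratio comes from an adjusted Cox model (minor efficiency and consistency point)

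*Protocol article*

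**What the plan says.** The Secondary outcomes section splits the work for time to death between two methods. For the test: "log-rank tests will be used to test for significant differences between the two treatment groups". No strata and no covariates are attached to it. For the estimate: "hazard ratios will be estimated with Cox proportional hazards regression, with a random effect for site and fixed effects for the exposure", with adjustment for the interval from vasopressor start (T0) to randomisation and for "vasopressor dose, APACHE III score at randomisation and type of shock".

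The same section cites Fig. 3 when it introduces the Kaplan-Meier curves and log-rank tests. The Fig. 3 legend names only the model: "Cox regression analysis with random effect for site and fixed effects for the exposure adjusted for the time between T0", followed by the remaining covariates.

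The other efficacy outcomes use one model for everything. Under Primary outcome, the test and the estimates share a source: "A two-sided *P*-value for the effect of treatment will be obtained from this model and values < 0.05 will be considered statistically significant". The 90-day mortality and MAKE-14 analyses follow that description, and RRT-free days use a proportional odds model with the same fixed and random effects. Allocation uses a "site stratified, permuted block randomisation method".

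**The concern.** A log-rank P value printed beside an adjusted Cox hazard ratio invites the reader to treat the two as one result, which they are not. The log-rank test addresses the marginal contrast between arms. The Cox hazard ratio is conditional on site and covariates. One can cross the 0.05 line when the other does not, and the article does not say how such a result would be presented.

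The second cost is precision. APACHE III, vasopressor dose, type of shock and time from T0 are collected at baseline and used in every other efficacy model. The declared test for these two outcomes does not use them. If they predict death, the test is less powerful than the model already planned beside it. Time to death is the only efficacy outcome handled this way, and the article gives no reason.

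**Working it through.** **Inputs from the article.** Total 1260; 20% control mortality at day 14; 6% absolute reduction, so 14% in the intervention arm; alpha 0.05, two-sided under Primary outcome; power 80%; attrition 2.5%; 1:1 allocation, stratified by site.

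**1. Reproduce the sample size.** Pooled-variance formula for two proportions, mean rate 0.17:

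n per arm = [1.960 × √(2 × 0.17 × 0.83) + 0.842 × √(0.20 × 0.80 + 0.14 × 0.86)]² / 0.06² = (1.041 + 0.446)² / 0.0036, about 614.1, rounded up to 615.

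Total 1230; 1230 / 0.975 gives 1262, against 1260 stated. The design figure reproduces.

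**2. Log-rank power on the same design.** With 2.5% attrition, about 614 per arm are evaluable. Under proportional hazards the implied marginal hazard ratio is ln(0.86) / ln(0.80) = 0.676. Expected deaths by day 14: 614 × (0.20 + 0.14) = about 209. Schoenfeld power: Φ(√(209/4) × |ln 0.676| − 1.96), which is 81%.

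**3. Compare the two tests by simulation.** The article gives no prognostic strength for the covariates, so it is assumed and varied. Setup: 1228 patients, about 36 per site, arms balanced within site, site SD 0.3 on the log-hazard scale, exponential survival censored at day 14, marginal mortality calibrated to 20% and 14%, 1500 replicates per setting. The Cox model adjusts for one correctly specified prognostic score, standing in for the four covariates, and omits the site term.

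| Log-hazard SD of score (assumed) | Log-rank power | Adjusted Cox power | Gain, points | Verdicts differ at 0.05 |
|---|---|---|---|---|
| 0 | 79.7% | 79.7% | 0.0 | 0.9% |
| 0.5 | 80.9% | 83.1% | 2.1 | 4.7% |
| 0.8 | 78.5% | 84.0% | 5.5 | 8.8% |
| 1.0 | 82.1% | 89.2% | 7.1 | 10.1% |
| 1.3 | 80.7% | 91.7% | 11.1 | 12.9% |

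The Monte Carlo standard error of each power is about 1 point. Gains are taken from unrounded powers.

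**4. Type I error.** With no treatment effect, the log-rank test rejects in 4.7% to 6.1% of simulated trials and the Cox test in 4.5% to 6.3%. Both sit near 5%.

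**5. The two methods address different quantities.** At the same 20% v 14% mortality, the conditional hazard ratio in the simulation moves from 0.674 (SD 0) to 0.618 (SD 1.3), while the marginal ratio is 0.676.

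**6. What site contributes.** A separate simulation compared a plain with a site-stratified log-rank test (35 sites, 18 v 18 per site, hazard ratio 0.676, site the only source of heterogeneity). Power was 80.9% for both at a site SD of 0.25, and 84.0% v 84.7% at 0.5. The gain in step 3 therefore comes from the covariates, not from site.

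Only the day-14 outcome was simulated, because the article gives no 90-day mortality assumption.

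**The case against.** Kaplan-Meier curves with a log-rank test, followed by an adjusted Cox hazard ratio, is a conventional and valid pairing. The log-rank test needs no covariate data, so no patient with survival data drops out. Time to death is secondary and largely re-expresses deaths already analysed at days 14 and 90 with the adjusted model. The article is also condensed: strata for the log-rank test may be set out in a fuller document that is not shown, so calling it unstratified and unadjusted is the plain reading of the text, not a quotation. All of this stands, and it limits the weight of the point.

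Three stronger readings are tempting, and the article supports none of them.

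- A reader might infer that two tests give two chances at significance and so inflate type I error. The text gives the test to the log-rank and the estimate to Cox. The chance that at least one falls below 0.05 (about 7% under no effect with a prognostic score) is not the error rate of the plan as written.
- A reader might infer that leaving out site is a serious fault because randomisation is site-stratified. Step 6 shows that stratifying changes almost nothing at plausible site variation.
- A reader might infer that the trial loses planned power. The 80% target belongs to binary 14-day mortality, whose analysis already adjusts for these covariates and site.

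The objection does not remove the mismatch between test and estimate, the departure from the trial's handling of its other efficacy outcomes, or the unused baseline information.

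**Conclusion.** The point holds as a minor one. For both time-to-death outcomes the declared test and the reported hazard ratio come from different analyses. Under the design effect at day 14 they would disagree on significance in about 5% to 13% of trials if the covariates have a log-hazard SD of 0.5 to 1.3, and in about 1% if they are not prognostic. The declared test forgoes about 2 to 11 points of power over that range, and none if the covariates carry no information; at an SD of 0.5 the gain is only about twice the Monte Carlo standard error.

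These sizes rest on an assumed prognostic strength, one well-measured score in place of four covariates, exponential survival, and no site term in the simulated Cox model. The upper end is optimistic for real covariates. The direction does not depend on the exact value, provided that the covariates predict death, which is plausible for APACHE III and vasopressor dose. The log-rank test itself is valid, and the primary analysis and sample size are untouched.

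**What to change.** State that the two-sided P value for time to death to day 14 and to day 90 is that of the treatment term in the prespecified Cox model with the random site effect and the four covariates. Keep the Kaplan-Meier curves, and label any log-rank test as descriptive. This also brings the text into line with the Fig. 3 legend.

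The cost is one sentence: no new data, no new model, no change in sample size, and the trial is still recruiting. The one small downside is that the Cox model needs complete covariates. The Missing data section does not expect missing values for APACHE III, type of shock or site; it does not mention vasopressor dose or time from T0, so completeness of those two at randomisation should be confirmed.
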